### Study procedures

Clinical assessment will be performed at admission (baseline), three, six months
and one year after treatment initiation. At each follow-up visit the surgeon
will perform a physical examination of both elbows and complete the MEPI and NRS
scores. Simultaneously, the patient will be sent a link to the online,
patient-specific DASH and OES questionnaires: this will be monitored by the
study coordinator. At the two weeks and twelve months follow-up visit an
anteroposterior and lateral radiograph of the elbow will be made. At the last
follow-up visit, an independent and blinded researcher will record any
interventions, complications and physical therapist visits.

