### Recruitment and consent

All adult patients with partial articular fractures of the radial head that
comprise ≥ 1/3^rd^ of articular surface,
have ≥ 2 millimeters of articular step-off but less than 2
millimeters of gap between the fragments presenting to either the emergency
department or the outpatient departments of the participating hospitals will be
invited to participate in the trial. The fractures are evaluated on standard
anteroposterior (AP) and lateral radiographs with optional Greenspan view. An
additional Computed Tomography (CT)-scan with axial, coronal and sagittal
reconstructions will be made for post-hoc analysis.

The treating surgeon or a member of the study staff will introduce and explain
the trial to the patient and address any questions the patient might have. The
patient will receive a written information form and a consent form. After
receiving informed consent, eligible patients will be randomized. We will use a
block randomization strategy with random blocksize and stratify for
participating country and age of the patients. Age groups will be 18-49 and
≥50 years old. Applicants will be allocated to either operative or
nonoperative treatment using a web-based randomization program. This web-based
program is secure and only members of the study staff have login credentials. It
is not possible to blind surgeons and patients for the allocated treatment.

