### Outcome measures

The primary outcome measure is the DASH outcome measure; a validated,
self-reported questionnaire designed to help describe the disability experienced
by people with upper-limb disorders and also to monitor changes in symptoms and
function over time [14-16].The DASH outcome measure is scored in two components: the
disability/symptom section (30 items, scored 1-5) and the optional high
performance Sport/Music or Work section (4 items, scored 1-5). The DASH gives a
score out of 100, in which a higher score indicates greater disability. The DASH
outcome score is validated in both the English and Dutch language.

Secondary outcome measures consist of;

– The Oxford Elbow Score (OES), which reflects both function and
pain following elbow surgery. The OES consists of three domains; pain, function
and social-psychological. Each domain comprises of 4 questions with 5 response
options per question. Each response is scored 0 to 4, with 0 representing
greater severity. Scores for each domain are calculated as the sum of each
individual item score within that domain. These scores are then converted to a
metric score between 0 and 100 (a lower score represents greater severity) [17,18].

– The Mayo Elbow Performance Index (MEPI), which is based on 4
domains (pain, range of motion, stability and elbow function). A total score
between 95 and the maximum 100 points is considered excellent; 80–95 is
good; 60–80 is fair and less than 60 points is poor [19].

– Elbow pain; Pain level will be determined using the Numeric
Rating Scale, an 11–point scale for patient self-reporting of pain

– Active and passive ROM (flexion, extension, pronation,
supination) of both elbow joints will be measured on both sides using a
universal goniometer.

– Crepitance or block to motion will be assessed with elbow and
forearm motion at admission and every follow up visit

– Number of complications (infection, neurovascular compromise,
subsequent or secondary intervention, arthrosis)

– Determining the need for and number of secondary
interventions

– Radiographic appearance of the elbow joint will be evaluated
on the anteroposterior and lateral radiographs at one year. Heterotopic
ossification will be classified as a bone exostosis or as soft tissue
ossification of a ligament, capsule or muscle (“myositis
ossificans”) according the classification scheme of Broberg and Morrey [20]; degenerative changes of the radiocapitellar and ulnohumeral joints

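### The pain NRS is defined as patient self-report, yet the unblinded surgeon completes it together with the MEPI, while the one blinded assessor is given none of the examiner-dependent scores

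*Protocol article*

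**What the plan says.** Four statements in the protocol article bear on who measures what.

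- **Outcome measures** describes the pain NRS as an 11-point "scale for patient self-reporting of pain". It describes the MEPI as built on four "domains (pain, range of motion, stability and elbow function"). For active and passive ROM it says that flexion, extension, pronation and "supination) of both elbow joints will be measured on both sides using a" goniometer, without naming the person who measures.
- **Study procedures** says that at each follow-up visit the surgeon "will perform a physical examination of both elbows and complete the MEPI and NRS" scores. In parallel the patient receives a link to the online "patient-specific DASH and OES questionnaires". The NRS is not part of that link.
- **Study procedures** also says that at the last "follow-up visit, an independent and blinded researcher will record any" "interventions, complications and physical therapist visits".
- **Recruitment and consent** says that it "is not possible to blind surgeons and patients for the allocated treatment".

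**Statistical analysis** then compares the MEPI, OES, NRS and ROM between the arms as secondary outcomes.

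**The concern.** A self-report scale is meant to carry the patient's rating without an intermediary. Here the protocol has a direct route to the patient, the online questionnaire, and leaves the NRS out of it. The score is completed by a clinician who knows the allocation.

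The MEPI and ROM depend on the examiner, and they too appear to rest with that clinician. A comparison of screw fixation with a sling cannot blind the surgeon, but it can blind an assessor, and the plan already provides for one. That person is not asked to examine the elbow or score anything that depends on an examiner's judgement.

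What is at stake is the credibility of the secondary comparisons of pain, elbow function as scored by the MEPI, and motion. A difference between arms in any of them, or its absence, could partly reflect who did the scoring.

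**Working it through.** The plan gives no figure on this point, so the check sets the sections side by side.

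**Step 1: who scores each continuous outcome in the analysis section.**

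| Outcome | Who scores it | Basis | Scorer blinded? |
|---|---|---|---|
| DASH (primary) | Patient, online | Stated, Study procedures | No |
| OES | Patient, online | Stated, Study procedures | No |
| Pain NRS | Surgeon completes it | Stated, Study procedures; self-report in Outcome measures | No |
| MEPI | Surgeon | Stated, Study procedures | No |
| ROM | Surgeon | Inferred | No, if the inference is right |

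The inference for ROM has three parts: the surgeon physically examines both elbows, ROM is measured on both sides and is a MEPI domain, and no other examiner is named.

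The count is 2 outcomes assigned to the surgeon by the text (NRS, MEPI) plus 1 by inference (ROM), so 3 of 5. The other 2 of 5, including the primary outcome, do not pass through the surgeon.

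**Step 2: overlap between outcomes.** Pain and ROM are both MEPI domains. An influence on how pain or motion is scored could therefore appear twice, once in its own outcome and once in the MEPI.

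**Step 3: can the two statements on the NRS be read together?**

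- *Reading A:* the surgeon assigns the number. This conflicts with the self-report definition.
- *Reading B:* the surgeon asks for the number and writes it down. This fits both sections, but the patient then states the rating to an unblinded clinician.

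The text does not choose between them. Under either reading the surgeon stands between the patient and the score, although a direct route exists.

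**Step 4: what the blinded researcher does.** The role is limited to the last visit and to three kinds of record. An intervention or complication tied to an implant or an operation would tell the researcher the arm. Physical therapist visits would reveal little, because the Intervention section opens them to both arms. So some of the recorded items may unblind the assessor, while ROM and the examined part of the MEPI, where blinding an examiner helps most, are not assigned to that person.

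**Step 5: size.** The document gives no standard deviation, expected difference or inter-rater data for the NRS, MEPI or ROM. Neither the size nor the direction of any bias can be calculated from it.

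**The case against.** The strongest reply is that nothing here is a true contradiction. One section says what the NRS is and the other says who fills in the form at the visit. A surgeon who notes the patient's spoken number satisfies both. That stands, and it reduces the NRS point from a contradiction to an unclear and avoidable mode of collection.

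The other objections, and what stands of each:

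- **ROM has no named assessor.** Correct. The ROM part is an inference and is labelled as one.
- **A blinded recorder of complications serves a purpose**, namely even ascertainment across arms. Correct. A reader might infer that blinding is wasted on items where it cannot hold. The documents do not show that: infection, neurovascular compromise and arthrosis are not all specific to one arm, nor are therapist visits.
- **The surgeons have no stated preference.** A reader might infer that they have a stake in the result, or that the protocol hopes for better motion after fixation. Ethical considerations says that no clear preference exists and that both treatments are in regular use at each institution. The Discussion sets possible better motion after fixation against a possibly higher risk of complications. Neither inference is supported. Nor does the text say that the scorer is the surgeon who operated; patients allocated to nonoperative care have no such surgeon.
- **The article is condensed, and assessor procedures may be in the full protocol.** This would answer a complaint about missing detail. It does not answer this point, because the article states who does what and the stated allocation can be improved.
- **Patients are unblinded as well.** True, and moving the NRS does not change that. It removes only the surgeon's influence.

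**Conclusion.** The point holds for secondary outcomes only. The NRS and MEPI are assigned by the text to an unblinded surgeon, and ROM is so by inference. The single blinded assessor is given other tasks, some of which may disclose the arm.

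A reader might go on to infer that the trial's main result is at risk. It is not at risk from this source: the primary DASH, like the OES, is completed online by the patient and is not affected by surgeon scoring.

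The conclusion rests on two assumptions: that the surgeon who examines the elbow also takes the goniometer readings, and that this surgeon knows the allocation, as Recruitment and consent implies. It is worth correcting because the change is cheap and uses an online form and a researcher that the plan already has.

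**What to change.** 1. **NRS.** Add the pain NRS as one item to the online form already sent with the DASH and OES, at every follow-up time, and delete the NRS from the surgeon's task under Study procedures. The cost is one extra question. The patient remains unblinded.
2. **ROM and MEPI at twelve months.** Where the independent blinded researcher can use a goniometer, have that person measure ROM and score the examined MEPI items (motion and stability) with both elbows covered, before taking any history. Interventions, complications and therapist visits are then recorded afterwards at the same visit, so nothing is lost. State in the text who assesses the MEPI and ROM and whether that person is blinded.
3. **Three and six months.** The MEPI and ROM stay unblinded at these visits. Report them as such.

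The cost is a few minutes per patient and brief goniometer training across the sites. Masking will be imperfect, and the MEPI pain and function items still depend on what an unblinded patient says. No additional visit or change in sample size is needed. The change does depend on the researcher being able to examine the elbow, which the article does not state.

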### Sample size calculation

The primary outcome variable will be the DASH, which has a minimal clinically
important difference of 17 for the elbow [16]. Consequently, a 2-sided unpaired T-test with an alpha-level of 0.05,
a beta-level of 0.1, and an allocation ratio of 1, requires 31 patients in each
group to detect an effect size of 0.85. Anticipating a dropout rate of 25%, a
sample size of 39 patients in each arm is required.

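### The 25% dropout allowance is added to the evaluable number instead of being divided out: 39 per arm leaves about 29 evaluable patients, not the required 31, and t-test power is 88.9% rather than 90%

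*Protocol article*

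**What the plan says.** The protocol article, Methods, Sample size calculation, sizes the trial on the one-year DASH score with a minimal clinically important difference of 17 points. The test is "a 2-sided unpaired T-test with an alpha-level of 0.05". The text continues with "a beta-level of 0.1, and an allocation ratio of 1, requires 31 patients in each" group "to detect an effect size of 0.85". It then anticipates that 25% of patients will drop out and concludes that a "sample size of 39 patients in each arm is required". The formula that turns 31 into 39 is not shown.

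Under Statistical analysis, the one-year DASH is to be compared by an analysis of covariance corrected for age, on an intention-to-treat basis. That section contains no second sample size or power figure.

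**The concern.** The 31 is the number per group needed in the analysis, and the 25% is the share of enrolled patients expected to be lost. The enrolment target should therefore leave 31 after a quarter have gone. A target of 39 appears too low for that, because a quarter of 39 is nearly 10.

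The recruitment target and its power are headline figures of the protocol. Ethics committees and readers will take 39 per arm as securing 90% power after 25% dropout. If it does not, the type II error under the plan's own assumptions is above the stated 0.1, and the stated target does not follow from its inputs.

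**Working it through.** **Inputs, all from the Sample size calculation section:** two-sided alpha 0.05; beta 0.1 (power 90%); allocation 1:1; standardised effect d = 0.85; 31 per group before dropout; dropout 25%; 39 per arm after dropout. The SD is not stated; 17 / 0.85 implies 20 DASH points.

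**Step 1: reproduce the 31.** For n per group, the power of the two-sided unpaired t-test comes from the noncentral t distribution with 2n − 2 degrees of freedom and noncentrality d × √(n/2). Solving for 90% power at d = 0.85 gives n = 30.08, which rounds up to 31. The plan's figure reproduces.

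**Step 2: reproduce the 39.**

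- Adding 25% to the evaluable number: 31 × (1 + 0.25) = 38.75, rounded up to 39. This matches the plan.
- Dividing by the retained share: 31 / (1 − 0.25) = 41.33, rounded up to 42. This does not match.
- Starting instead from the normal-approximation size of 30: 30 / 0.75 = 40, still above 39. In any case the plan's own base is 31.

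Of the routes tried, only adding 25% to the plan's 31 gives 39.

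**Step 3: what 39 per arm leaves.** 39 × 0.75 = 29.25, so about 29 evaluable per arm, 2 short of 31. Retaining 31 of 39 allows a loss of 8 / 39 = 20.5%, not 25%. With 42 per arm, 42 × 0.75 = 31.5, which restores the 31.

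**Step 4: power at d = 0.85, two-sided t-test.**

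| Evaluable per arm | Power | Type II error |
|---|---|---|
| 31 | 90.9% | 9.1% |
| 30 | 89.9% | 10.1% |
| 29 | 88.9% | 11.1% |

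If dropout is random, with each patient lost independently with probability 25% (an assumption), power averaged over the possible arm sizes is also 88.9%. Under the same assumption, an arm of 39 retains at least 31 patients about 33% of the time, against about 65% for an arm of 42.

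**Step 5: size of the shortfall.** In recruitment: 42 − 39 = 3 per arm, 6 in total, and 6 / 84 is about 7%. In detectable effect: 29 per arm gives 90% power at d = 0.866. With the implied SD of 20 that is 0.866 × 20 = 17.3 DASH points, against the stated 17.

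**The case against.** The arithmetic is not in dispute; the objection is to how much it matters.

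- **The loss is about one point of power.** Rounding 30.08 up to 31 had already built in nearly one patient of slack, so against the 90% target itself the deficit is about one patient per arm. A shift in detectable difference from 17 to 17.3 points changes no design decision. This stands, and the point should not be presented as a threat to the trial's validity.
- **The inputs are less certain than the error is large.** Taking SDs of 19 and 21 as assumptions, 29 per arm would give 91.7% power at an SD of 19, while even 31 per arm would give only 88.0% at an SD of 21. The 25% dropout is itself a planning guess. This is true, but uncertain inputs do not make a wrong calculation from them right.
- **The primary analysis is an age-adjusted ANCOVA, not a t-test.** If age and DASH correlated at 0.1, 0.2 or 0.3 (assumed values), power at 29 per arm would be 89.2%, 90.1% or 91.5%. So the shortfall against 90% is shown for the unadjusted t-test only, and that qualification should be kept. The protocol gives no such correlation and bases its size on the t-test, so the adjustment does not repair the stated calculation.
- **The multiplication by 1.25 is inferred.** The protocol shows no formula, so this rests on the numerical match. The finding does not depend on it: 39 × 0.75 falls short of 31 however 39 was reached.

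Nor is this a detail that a condensed article leaves to a fuller document. Both inputs and the result are printed, and they disagree.

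**Conclusion.** The concern holds. The 31 per group is right for the stated test and effect size; the 39 per arm is not right for 31 evaluable patients with 25% dropout. The correct figure is 42 per arm. With 39 and the plan's own dropout rate, about 29 per arm remain, t-test power is 88.9%, and the type II error is about 11% instead of 10%.

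The effect on power is small and the trial stays close to its planned level. The case for correcting the figure rests on the certainty of the error, its place in a number the trial relies on, and the low cost of putting it right. The conclusion assumes that 25% means a quarter of enrolled patients without a one-year DASH score. The power figures assume d = 0.85 and the unadjusted two-sided t-test used for sizing.

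**What to change.** Correct the last sentence of the Sample size calculation section in one of three ways:

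- **(a)** Keep 39 per arm and state that 25% dropout leaves about 29 evaluable patients per arm, with about 89% power for an effect size of 0.85.
- **(b)** Keep 39 per arm and state that the tolerated dropout is about 20%, which retains 31 per arm (39 × 0.80 = 31.2).
- **(c)** If 31 evaluable patients and 25% dropout are both to be kept, state 42 per arm, 84 in total.

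Options (a) and (b) cost one sentence and no patients; the price is a slightly lower stated power or a lower stated dropout allowance. Option (c) costs 6 more patients, about one and a half months at the 4 per month expected in the Discussion (6 / 4 = 1.5).

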### Statistical analysis

Normality of continuous data will be tested with the Shapiro-Wilk and
Kolmogorov-Smirnov test as well as by inspecting the frequency distributions
(histograms). Homogeneity of variances will be tested using the Levene’s
test. The analysis will be performed on an intention to treat basis. Patients
with protocol violations will remain in follow-up, and data will be recorded.
Data will be analyzed with and without inclusion of patients with a protocol
violation. Descriptive analysis will be performed to report baseline
characteristics in both treatment groups. For continuous data (e.g. age), means
and standard deviations (parametric data) or medians and percentiles
(nonparametric data) will be calculated. For categorical data (e.g. gender)
frequencies will be calculated.

Patients will be analyzed according to the intention-to-treat protocol. The
primary outcome, DASH at one year will be corrected for age and assessed using
an analysis of covariance (ANCOVA). Trends in DASH scores among the different
time points will be assessed using a repeated measures ANOVA if the data is
normally distributed. The secondary outcomes; MEPI, OES, pain as indicated on a
Numerical Rating Scale (NRS), Range of Motion (ROM) will be analyzed in a
similar manner. The radiological outcome, number of conversions and complication
rate will be determined using either a Fisher Exact or a Chi square test,
depending on the order of magnitude of the results.

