## Methods

### Study design

The RAMBO trial is a prospective, international multicenter, randomized
controlled trial. Two academic and six teaching hospitals in the Netherlands as
well as a teaching hospital in the United States and a teaching hospital in
Canada will participate.

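### Randomisation is stratified by country and age, but the primary ANCOVA corrects for age only; if country predicts DASH, the interval is slightly too wide

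*Protocol article*

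**What the plan says.** Under Recruitment and consent, the protocol article describes a "block randomization strategy with random blocksize and stratify for" "participating country and age of the patients", with age split at 50 years. Study design lists three countries. The Dutch part is described as "Two academic and six teaching hospitals in the Netherlands as" "well as a teaching hospital in the United States and a teaching hospital in" Canada, so eight of the ten hospitals are Dutch and the other two countries have one each.

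Under Statistical analysis, the "primary outcome, DASH at one year will be corrected for age and assessed using" analysis of covariance. No other covariate is named. MEPI, OES, pain and range of motion follow the same approach: "Numerical Rating Scale (NRS), Range of Motion (ROM) will be analyzed in a" similar manner.

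The sample size rests on "a 2-sided unpaired T-test with an alpha-level of 0.05", 90% power and an effect size of 0.85, with no credit for stratification or covariates.

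**The concern.** The two sections do not match. One stratification factor is in the model and the other is left out, without a reason. Because the article names its covariate, this is a stated choice and not a detail left open.

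Stratified blocks keep the arms nearly balanced within each country, so differences in DASH between countries largely cancel from the treatment contrast. A model without country still counts those differences as residual noise. If they exist, the reported standard error exceeds the true sampling variation, the confidence interval is wider than it need be, and the test rejects slightly less often than 5% under the null. Part of the precision that stratification provides is then lost in a small trial. The continuous secondary outcomes inherit the same loss.

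**Working it through.** **The plan's own figure.** The inputs from Sample size calculation are a difference of 17 DASH points, an effect size of 0.85, two-sided alpha 0.05, power 90% and 1:1 allocation.

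- Implied SD: 17 / 0.85 = 20 points.
- Normal approximation: n = 2 × (1.960 + 1.282)² / 0.85² = 29.1, so 30 per arm.
- Exact t-test power: 89.9% at 30 and 90.9% at 31. The stated 31 reproduces.
- With 39 enrolled per arm and 25% loss, 39 × 0.75 = 29.25, so about 29 per arm are evaluable. Exact power at 29 is 88.9%.

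**Assumption.** The documents give neither a country effect on DASH nor patient numbers by country. Let R² be the share of 12-month DASH variance explained by country, and vary it.

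**Analytic size.** With perfect balance within country, the age-only standard error is too large by the factor 1/√(1 − R²). The real type I error is then 2 × [1 − Φ(1.96 / √(1 − R²))].

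| R² | SE factor | Real type I error |
|---|---|---|
| 0 | 1.000 | 5.0% |
| 2% | 1.010 | 4.8% |
| 5% | 1.026 | 4.4% |
| 10% | 1.054 | 3.9% |

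**Power at 29 per arm.** Both models must be judged against the same country effect. The true sampling SD of the estimate is reduced by √(1 − R²) under either model, because the reduction comes from the design. The age-only model only applies a critical value that is too large by the SE factor. The noncentral t distribution, with noncentrality (0.85 / √(1 − R²)) × √(29/2), gives:

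| R² | Age only | Age and country | Gain |
|---|---|---|---|
| 5% | 89.5% | 90.4% | 0.9 points |
| 10% | 90.0% | 91.8% | 1.8 points |

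**Simulation with imperfect balance.** The settings were SD 20, blocks of 2, 4 and 6 within country by age group, and a country mix of either 80/10/10 or equal thirds. Block sizes and mix are assumptions. The table gives the ratio of 95% interval widths, age-only over age plus country.

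| R² | 62 evaluable | 78 randomised, 58 evaluable |
|---|---|---|
| 0 | 0.99 to 1.00 | 0.99 |
| 2% | 1.004 to 1.009 | about 1.00 |
| 5% | 1.02 to 1.03 | about 1.02 |
| 10% | 1.05 to 1.06 | about 1.05 |

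At R² = 10% with 62 patients, the mean full width falls from about 19.8 to between 18.7 and 18.9 DASH points. At R² = 0, adding country widens the interval by at most about 1%.

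**What the assumed R² means in DASH points.** For a contrast of the Netherlands against the rest, with a fraction p of patients outside the Netherlands, the gap is 20 × √(R² / [p(1 − p)]).

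- If patients follow hospitals (p = 0.2): 2% needs 7.1 points, 5% needs 11.2 and 10% needs 15.8.
- With equal thirds (p = 2/3): 5% needs 9.5 points and 10% needs 13.4.

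**The case against.** The strongest reply is that the loss may be close to nothing. It exists only if country predicts DASH, and no country effect is reported. An R² of 10% would need a gap of almost 16 points if patients follow the hospitals, close to the 17-point minimal clinically important difference. Entry is limited to one narrowly defined isolated fracture, and the article says the DASH is validated in English and Dutch. A share of 0% to 2% is at least as compatible with the documents. This stands, and it is why the point has to be worded conditionally.

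A second reply is that a three-level country factor may be awkward with one hospital each in the United States and Canada. This also stands and is met by a pooling rule.

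A third is that a fuller covariate list may sit in a document not shown. That weakens the point but does not remove it, because the article names age as the correction.

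A reader might infer more than the documents support, in three ways:

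- **That the intervals are too wide as a matter of fact.** They are so only if country is prognostic.
- **That the primary result would be invalid.** The effect estimate is unbiased and the error is on the conservative side.
- **That planned power is lost, or that adjustment lifts it from 88.9% to as much as 91.8%.** The sample size is a plain t-test that takes no credit for stratification. The 88.9% figure also ignores the benefit that stratification already gives the age-only estimate when country matters, so that comparison overstates the gain.

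**Conclusion.** The point holds in a limited form. The mismatch between the stratification and the primary model is plain in the text and extends to the continuous secondary outcomes. Its consequence depends on an unstated country effect: negligible for R² up to about 2%, and a modest loss of precision at 5% to 10%, within the power gains tabulated above. The upper end rests on country gaps that nothing in the documents suggests. Even there, the direction is conservative. The reason to act is that alignment with the design is nearly free, and that fixing the model now avoids a later choice between two analyses.

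**What to change.** State the primary model as an ANCOVA of 12-month DASH on treatment, age and country, with country as used for randomisation. Add a rule, fixed before the outcome data are seen, for pooling the United States and Canada into one non-Dutch category if either contributes few patients. Use the same covariates for MEPI, OES, NRS and range of motion.

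The cost is a line or two of analysis text and two degrees of freedom, or one if the small countries are pooled. Country is already recorded for randomisation, so no new data are needed and the sample size does not change.

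### The 12-month ANCOVA and the repeated measures ANOVA make no use of 3- and 6-month DASH scores from patients lost later, although 25% dropout is expected; one mixed model on all scores would use them

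*Protocol article*

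**What the plan says.** All references are to the protocol article.

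- **Study procedures** sets the visits: "Clinical assessment will be performed at admission (baseline), three, six months" and one year. The patient is sent the online DASH at each follow-up visit, so many patients who are later lost will already have given 3- or 6-month scores.
- **Sample size calculation** expects losses: "Anticipating a dropout rate of 25%, a" total of 39 per arm is planned.
- **Statistical analysis** states the principle: "Patients will be analyzed according to the intention-to-treat protocol. The" primary outcome, DASH at one year, is then given an ANCOVA with age as the only named covariate.
- The DASH course is a separate analysis. Trends across the "time points will be assessed using a repeated measures ANOVA if the data is" normally distributed. No method is named for the other case. The continuous secondary outcomes (MEPI, OES, pain, range of motion) are to be handled similarly.

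**The concern.** Two features of the named methods matter once a quarter of the patients may be lost.

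First, an ANCOVA of the 12-month score on treatment and age has no place for earlier DASH scores. A patient who answers at 3 and 6 months and is then lost contributes nothing to the primary estimate. Classical repeated measures ANOVA goes further and by default drops anyone with a missing visit.

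Second, the trend analysis depends on normality of a score bounded at 0 and 100. If normality fails, the stated rule leaves no analysis of the course.

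Precision is at stake, and in some circumstances bias. Surgeons and patients are not blinded and the arms differ in burden, so dropout could relate to recovery differently by arm. The interim scores that would partly correct for this are already being collected.

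**Working it through.** **Inputs from Sample size calculation.** The difference is 17 ("important difference of 17 for the elbow"). The test is "a 2-sided unpaired T-test with an alpha-level of 0.05". Power and allocation: "a beta-level of 0.1, and an allocation ratio of 1, requires 31 patients in each" group. The standardised effect is 0.85 ("group to detect an effect size of 0.85"). Implied SD = 17 / 0.85 = 20.

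**Assumed, not in the article.** Correlation r between 6- and 12-month DASH of 0.7 (0.5 as an alternative), the form of dropout, and the rate of missed interim visits.

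**1. The plan's own figures.** The exact noncentral t calculation gives power 0.899 at 30 per arm and 0.909 at 31, so 31 is reproduced. The 39 is 31 × 1.25 = 38.75, rounded up. (Whether that is the right inflation is a separate matter.)

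**2. Patients with a 12-month DASH.** 39 × 0.75 = 29.25, about 29 per arm. Patients who missed only an interim visit stay in the primary ANCOVA.

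**3. Patients with every visit (trend analysis only).** If a further 5%, 10% or 15% are missing independently at each of 3 and 6 months:
- 39 × 0.75 × 0.95² = 26.4
- 39 × 0.75 × 0.90² = 23.7
- 39 × 0.75 × 0.85² = 21.1

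**4. Precision under random dropout,** if all dropouts gave a 6-month score.
- Completers: SE = 20 × √(2/29.25) = 5.23.
- Likelihood-based, using the 6-month score: SE = 20 × √[(2/29.25) × (1 − 0.25r²)] = 4.90 at r = 0.7 and 5.06 at r = 0.5.
- Gain: 4.90/5.23 = 0.94, about 6% smaller; 5.06/5.23 = 0.97, about 3% smaller.

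**5. Bias in the completers' 12-month difference.** Let z be the standardised 6-month score and let the log-odds of dropout change by 1 per SD of z, with 25% lost. Bias in one arm = r × SD × mean of z among those who stay. Numerical integration gives a mean of 0.213 in absolute value.

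| Dropout pattern | True difference | Bias in the difference |
|---|---|---|
| Random | any | 0 |
| Same in both arms | 0 | 0 (cancels) |
| Same in both arms, better-recovered patients leave | 17 | about 1.5, towards no effect |
| Opposite by arm | 0 | 2 × 0.7 × 20 × 0.213 = 6.0 (4.3 at r = 0.5) |

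For the third row, assume the arms also differ by 17 points (0.85 SD) at 6 months. Loss is then 18% in one arm and 32% in the other, the means of z among stayers (each from its own arm mean) are 0.160 and 0.266, and 0.7 × 20 × (0.266 − 0.160) = 1.5.

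A simulation with steeper dropout (log-odds 1.2 per SD) agrees. With the same pattern in both arms, completers gave 15.4 when the truth was 17. With opposite patterns they gave 7.1 when the truth was 0 and 22.4 when it was 17. The likelihood-type estimate gave 16.9, 0.0 and 17.0.

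**6. How far the alternative helps.** Those near-zero biases hold because dropout in the simulation depends only on a score that everyone gave. Under the opposite pattern with no true effect:
- Half the dropouts leave before giving a 6-month score: 2.6 points of bias remain, against 6.0 for completers.
- All leave before it: 6.0 for both.
- Dropout depends on the 12-month state itself, with every 6-month score seen: about 4.7 against 8.6.

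**The case against.** The strongest reply is that this is a missing-data point in disguise. The article does not say that partial data will be discarded, and imputation may be specified in a full protocol or analysis plan. That stands as far as it goes: the absence of a missing-data section is not the criticism. The criticism concerns the two models the article does fix, which as named make no use of interim scores from patients lost later.

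Second, an age-adjusted ANCOVA at one prespecified time is a recognised primary analysis, and the precision gain is small. Both are true. The ANCOVA is not an error. The mixed model does better with data already in hand.

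Three stronger readings are tempting, and the article does not support them.

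- *The primary analysis is biased.* Nothing in the article says how dropout will relate to recovery. Opposite patterns by arm are plausible in an unblinded trial but are an assumed adverse case. Nor does every link between dropout and recovery bias the comparison: the same pattern in both arms cancels when there is no effect.
- *The primary analysis shrinks to about 24 per arm.* Deletion for any missing visit and the normality condition belong to the trend analysis, not to the primary ANCOVA. The 24 also rests on an assumed 10% missing at each interim visit.
- *Intention to treat is contradicted.* The section uses the term in connection with allocation and protocol violations. An ANCOVA of observed outcomes does not breach it in that sense.

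**Conclusion.** The point holds as a choice of method that can be improved, not as a demonstrated bias. At the anticipated loss, about 29 of 39 per arm enter the primary analysis, and the interim scores of the other 10 or so are unused. The trend analysis would keep fewer, and it has no stated method if normality fails.

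With the implied SD of 20 and an assumed correlation of 0.7, bias in the 12-month difference runs from 0 through about 1.5 points to about 6 points. The last is about a third of the 17-point minimal important difference (6.0/17 = 35%) and arises only when dropout patterns oppose each other by arm. Under random dropout the cost is precision alone, a standard error of 5.2 where 4.9 is attainable.

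A likelihood-based model removes dropout bias only if data are missing at random given the observed scores. It helps only in part, or not at all, for patients who leave before giving a 3- or 6-month score. The article does not say when dropout is expected.

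**What to change.** - Fit one linear mixed model to the 3-, 6- and 12-month DASH with treatment, visit, treatment-by-visit, age group and country (the two stratification factors), and an unstructured covariance.
- Take the 12-month treatment contrast as the primary estimate and let the interaction describe the course.
- Drop the normality condition. If residuals are skewed, give a bootstrap confidence interval.
- Keep the age-adjusted 12-month ANCOVA as a sensitivity analysis.
- Treat the continuous secondary outcomes in the same way.
- State that the model assumes data missing at random given the observed scores, and that early leavers limit what it can correct.

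The cost is analysis wording and slightly more complex modelling. No new data or visits are needed.
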